## Abstract

**Background:**

Qihuang needle therapy is a newly developed acupuncture therapy to treat tic disorders in clinical practice. However, the mechanism to reduce tic severity remains unknown. Changes in intestinal flora and circulation metabolites are perhaps the potential pathogenesis of tic disorders. As a result, we present a protocol for a controlled clinical trial using multi-omics analysis to probe the mechanism of the Qihuang needle in managing tic disorders.

**Methods:**

This is a matched-pairs design, controlled, clinical trial for patients with tic disorders. Participants will be allocated to either an experimental group or a healthy control group. The main acupoints are Baihui (GV20), Yintang (EX-HN3), and Jueyinshu (BL14). The experimental group will receive Qihuang needle therapy for a month, while the control group will receive no interventions.

**Expected outcomes:**

The change in the severity of the tic disorder is set as the main outcome. Secondary outcomes include gastrointestinal severity index and recurrence rate, which will be calculated after a 12-week follow-up. Gut microbiota, measured by 16S rRNA gene sequencing; serum metabolomics, assessed *via* LC/MS; and serum zonulin, assessed by enzyme-linked immunosorbent assay (ELISA), will be used as biological specimen analysis outcomes. The present study will investigate the possible interactions between intestinal flora and serum metabolites and the improvement of clinical profiles, which may elucidate the mechanism of Qihuang needle therapy for tic disorders.

**Trial registration:**

This trial is registered at the Chinese Clinical Trial Registry (http://www.chictr.org.cn/). Registration number: ChiCTR2200057723, Date: 2022-04-14.

## 1. Introduction

Tic disorders are neurodevelopmental disorders characterized by recurrent motor and/or vocal tics (1). The Diagnostic and Statistical Manual of Mental Disorders, Fifth Edition (DSM-5) (2), defines the following five tic disorders: provisional tic disorder; persistent (chronic) motor or vocal tic disorder; Tourette's disorder (also known as Tourette's syndrome [TS]); other specified tic disorder; and unspecified tic disorder. Tic disorders are common in China, with a prevalence of transient tic disorder (TTD), chronic tic disorder (CTD), and Tourette syndrome (TS) of 1.7, 1.2, and 0.3%, respectively (3).

Tics usually begin between the ages of 3 and 8 years and become worse between the ages of 8 and 12 years for most patients. The first tic symptoms are usually simple motor tics, restricted to one muscle or a single muscle group. Tics then progress to involve more muscle groups or present with mimicking. Simple vocal tics, demonstrating meaningless sounds, usually occur after motor tics. For children or adolescents, the features of tics wax and wane in severity and frequency, and new tic symptoms replace, combine with, or even exacerbate the old ones (4, 5). Academic stress and family pressure may increase the incidence of tic disorders among school-age children. Excessive attention from parents, ridicule from peers, or incomprehension from teachers contribute to the aggravation of tics. Despite reports that tics tend to mitigate spontaneously throughout adolescence and reach complete remission in early adulthood, tics do not always remit within a year in most children with recent-onset tic disorders, and recurrence may occur even after long-term remission among patients with CTD (6). Attention-deficit hyperactivity disorder, obsessive-compulsive disorder, and autism spectrum disorder are the most common psychiatric comorbidities that impair social, behavioral, or emotional functioning (7).

Psychoeducation is recommended as the initial intervention, and behavior therapy is recommended as a first-line intervention for children and adults with CTD or TS (8). Nevertheless, education and behavior therapy are aimed at older patients or children with insufficient evidence to prove effectiveness and safety (9). Pharmacotherapy is recommended as the second option but may cause considerable adverse effects (10). Furthermore, for refractory tic disorders, surgical interventions using deep brain stimulation have been suggested as an alternative option (11), but the efficacy and safety thereof are non-conclusive. Although various neural regulation therapies, such as repetitive transcranial magnetic stimulation (rTMS), cranial electrotherapy stimulation, and electroencephalographic biofeedback, have been used in clinical practice, the effects of such treatments are still a matter of debate (5). Thus, a therapeutic strategy for tic disorders is required.

A growing body of evidence has proven that acupuncture is an effective treatment for tic disorders (12, 13). Acupuncture, especially electroacupuncture or scalp acupuncture alone, demonstrates a positive effect in terms of total clinical effectiveness rate, the incidence of adverse events, and recurrence. Currently, common methods of acupuncture treatment for tic disorders include traditional Chinese medicine acupuncture, electroacupuncture, scalp acupuncture, and auricular acupuncture (14). However, these methods have some disadvantages, such as long-time needle retention, challenges in electric current control, or the necessity for the child to take the initiative. In addition, most patients are school-aged children with academic pressure, requiring short-course therapies with flexible treatment times.

Qihuang (QH) needle, invented by [name], is a new acupuncture instrument developed from the Jiuzhen (Nine Needles) created in ancient times (15). Qihuang needle therapy (QHN therapy) absorbs the essence of the meridian sinew theory and the “five thorns” that originated from the Inner Canon of Huangdi (16). QHN therapy has advantages compared with traditional acupuncture (17). First, it is less painful, with almost no pain when the needle punctures the skin. Second, the manipulation of the QH needle is swift, without needle retention. Third, point selection is simple and usually involves no more than five acupoints in one treatment session. Finally, the treatment period is shorter than traditional Chinese acupuncture, especially for intractable pain.

Recently, several cases that investigate the clinical efficacy of QHN therapy for various kinds of diseases such as low back pain (18, 19), acute gouty arthritis (20), and Parkinson's disease (21) have been reported. QHN therapy has been used in the field of pediatric neuropsychiatric disorders such as tic disorders (22) and spastic hemiplegic cerebral palsy (23). QHN therapy seems to be a potential treatment method for tic disorders, and further studies exploring its efficacy and mechanisms are needed.

Tic generation is caused by dysfunction of the cortico-basal ganglia neuronal networks (24). Changes in the gut microbiota could serve as a significant or moderating factor in the etiology of basal ganglia-associated diseases, such as tic disorders. A descriptive model of the microbiota-gut-brain axis in tic disorders has been reported (25, 26): genetic and environmental factors alter the gut microbial composition and its activity; disturbances in intestinal flora induce escalation of gastrointestinal permeability; and intestinal-derived molecules may pass into the peripheral circulation and permeate into the brain through the damaged blood-brain barrier, which may cause altered basal ganglia function. The gut microbial alteration may lead to other risk factors, including altered short-chain fatty acid levels, increased vagal stimulation, and the release of other bacterial metabolites. Zonulin is a human protein that could reversibly regulate intestinal permeability (27). Increased zonulin indicates impaired gut barrier integrity, and serum zonulin has been applied as a peripheral biomarker to assess human intestinal barrier permeability in neurological or mental diseases to explore the roles of dysbiosis and gut barrier integrity (28, 29). Under the hypothesis that intestinal-derived molecules penetrate the gut barrier into the peripheral circulation, corresponding molecular changes could be assessed *via* serum metabolomics. In addition, the interaction between the gut microbiome and serum metabolites can be explored to identify some previously unknown links between intestinal microbiota alterations, circulating metabolites, and physical disorders (30, 31).

Most studies regarding the mechanism of acupuncture therapy for tic disorders are conducted *via* animal model experiments, which focus on acupuncture regulating neurotransmitters (32, 33). Studies investigating the mechanism in the clinical context are insufficient. Recently, omics analyses have been used as prospective methods to probe acupuncture mechanisms in the clinical context. Using gut microbiome sequencing, acupuncture was found to modulate the structures and diversity of the gut microbiome, inhibit inflammation of the central nervous system (34, 35), gradually improve gut barrier function, and regulate neurotransmitters (36, 37) in various neuropsychiatric diseases. As for metabolomics assays, the potential mechanisms of acupuncture to treat neuropsychiatric disorders may be associated with modulating systematic inflammation and improving lipid metabolism (38–40). QHN therapy shows effectiveness in the treatment of tic disorders in clinical practice and is worth investigating to determine the specific mechanism. Nevertheless, omics studies of tic disorders are in their infancy (25, 41), with few studies on acupuncture. We aimed to determine how QHN therapy works in the treatment of tic disorders by investigating how it influences the gut microbiota and serum metabolites in children with tic disorders and to analyze possible correlations between clinical profiles and the changes in the gut flora and serum metabolites.

## 2. Methods and analysis

### 2.1. Study design and participants

This is a matched-pairs design, controlled, clinical trial with two groups (experimental group and healthy control group). Patients with tic disorders and age–gender-matched healthy children will be recruited through advertisements posted on web pages and display boards or through the outpatient system recommended by doctors at Panyu Hospital of Chinese Medicine (Guangzhou, China) and Foshan Fosun Chancheng Hospital (Foshan, China). Both hospitals are tertiary hospitals. All participants will be screened according to the inclusion and exclusion criteria. The guardians of eligible participants will sign a written informed consent (see Supplementary material 1) after a detailed explanation of the study by the investigators and will be provided with a baseline assessment. Participants are free to withdraw from the study at any time. This protocol was designed according to the Standard Protocol Items: Recommendations for Interventional Trials (SPIRIT) guidelines (42) and the Standard Protocol Items for Clinical Trials with Traditional Chinese Medicine 2018: Recommendations, Explanation, and Elaboration (SPIRIT-TCM Extension 2018) (43). The study was registered in the Chinese Clinical Trial Registry (ChiCTR2200057723).

### 2.2. Eligibility criteria

Participants must fulfill the diagnostic criteria for provisional tic disorder and persistent motor or vocal tic disorder according to the DSM-5 (2). Patients will be screened according to the inclusion and exclusion criteria listed in Table 1.

**Table 1 T1:** Eligibility criteria.

	**TD patients**	**Healthy controls**
Inclusion Criteria	1. Aged between 4 and 18 years	1. Matched age, sex, family history of a psychiatric condition, parental marital status, mode of delivery and birth weight to the TD group^*^
	2. Meeting the diagnostic criteria of transient tic disorder and Persistent Motor or Vocal Tic Disorder according to the Diagnostic and Statistical Manual of Mental Disorders, Fifth Edition (DSM-5) (1, 2)	2. No current or history of head trauma, convulsions, epilepsy, growth and development disorders, mental illness, digestive system disease, abdominal operation or asphyxia at birth
	3. The course of a provisional tic disorder is more than 3 months	3. No current or history of medication of mental disorders especially drug influencing neurotransmitters
	4. The score of YGTSS >12	4. The mother is healthy during pregnancy (no history of infection, digestive system disease, trauma or taking any medication)
	5. Have not received acupuncture or moxibustion within 3 months, and drug withdrawal period ≥12 weeks	
	6. Guardians are willing to sign the informed consents	
Exclusion Criteria	1. Secondary tic disorders	
	2. Patients with severe diseases of important organ systems: liver and kidney damage, cardiovascular insufficiency, metabolic diseases, malignant tumors, etc., which may adversely affect our clinical observation	
	3. Obsessive-compulsive disorder, depression, Attention deficit hyperactivity disorder, anxiety, autism spectrum disorder, eating disorder, or a history of substance abuse	
	4. Epilepsy, Huntington's disease, rheumatic chorea, hepatolenticular degeneration, substantia nigra degeneration, psychogenic tics and other extrapyramidal disorders	
	5. The use of antibiotics, probiotics, high-dose vitamin or immunomodulatory medications within 4 weeks before the fecal sample collection	
	6. Conditions like any infective diseases or other severe disorders that may influence the gut microbiota	
	7. Ulcers or surgical scars on the acupoint area	
	8. Children who are participating or participated in other clinical trials within 1 month	
Withdrawal criteria and management	1. Misdiagnosis, violation of the inclusion criteria	
	2. Self-use of prohibited treatment	
	3. Poor cooperation with the established treatment or data collection procedures	
	4. Serious adverse events or life-threatening diseases or an acute progression of the disease occurs during the trial	
	5. Obvious discomforts arise because of the therapy	
	6. Participants request withdrawal voluntarily	

American Psychiatric Association (1).

* Healthy control matching procedure: To select a healthy control group comparable in size to the experimental group. The criteria used for this procedure (with match tolerance) are as follows: (1) age (±1 year), (2) sex (exact match), (3) family history of the psychiatric condition (exact match), (4) parental marital status (exact match), (5) mode of delivery (exact match), and (6) birth weight (±100 g). We chose to match these variables as they may be the risk factors influencing the development of tic disorders.

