### 2.3. Sample size

Considering that the focus of omics studies is the mechanism of the intervention effect, the sample size estimation of our exploratory research is distinctive compared with classical randomized control trials. Given previous literature regarding the omics analysis of acupuncture (44–46), at least 15 participants in each group are required. Thus, we set at least 15 participants in each group in the present design. Allowing for a 20% dropout rate, we plan to recruit 40 participants (20 participants per group).

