### 2.5. Outcome evaluations

The clinical evaluations include the assessment of the severity of tics and gastrointestinal symptoms. The recurrence rate will be measured after a 12-week follow-up. The primary outcome measure will be the Yale Global Tic Severity Scale (YGTSS), and secondary outcomes will consist of the gastrointestinal severity index (GSI) and the recurrence rate. Biological specimen analysis outcomes will include changes in the composition of intestinal microbiota, serum metabolites, and serum zonulin. YGTSS and GSI will be assessed at baseline and after 4 weeks when the interventions have been completed. Data relating to the recurrence rate will be collected after a 12-week follow-up. Feces and serum samples will be collected at baseline and 4 weeks after the interventions. If sample collection is concurrent with a treatment, sample collection will be performed after all interventions have been completed. The feces sample will be collected as soon as possible after completing all interventions.

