### 3.1. Statistical analysis

#### 3.1.1. Clinical data and serum zonulin

For the clinical data, statistical analyses will be performed using SPSS Statistics 24.0 (IBM SPSS Statistics, Armonk, NY). Children in the experimental group will be matched to their peers in the healthy control group on age, sex, family history of a psychiatric condition, parental marital status, mode of delivery, and birth weight. Categorical variables will be described in the form of frequencies or percentages. Continuous variables will be presented as mean ± standard deviation or median and range. The chi-square test or Fisher's exact test will be used to compare the change in the categorical variables. Changes in YGTSS, GSI, and concentration of serum zonulin in the experimental group before and after treatment will be analyzed using paired sample *t*-test if the data conform to a normal distribution. The Wilcoxon paired-samples signed-rank test will be performed if the data do not conform to normal distribution or if there are differences in variance uniformity. Differences in concentration of serum zonulin between two matched groups at baseline will be analyzed with the above statistical methods. The results are based on two-sided tests, and a *P*-value of <0.05 will be considered statistically significant.

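### Unless children withdrawn for acute progression are still scored and analysed, the before-after YGTSS change can be biased toward benefit

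*Protocol article*

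**What the plan says.** The withdrawal row of Table 1 (section 2.2) gives six grounds. Three bear on how the child is faring or on the treatment received: "Serious adverse events or life-threatening diseases or an acute progression of the disease occurs during the trial", "Obvious discomforts arise because of the therapy" and "Self-use of prohibited treatment". The other three are misdiagnosis or breach of the inclusion criteria, poor cooperation with treatment or data collection, and voluntary request. The row's label promises management as well as criteria, but only criteria follow.

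Section 2.5 names the YGTSS as the primary outcome measure and sets its timing: "YGTSS and GSI will be assessed at baseline and after 4 weeks when the interventions have been completed". Section 3.1.1 gives the test: "Changes in YGTSS, GSI, and concentration of serum zonulin in the experimental group before and after treatment will be analyzed using paired sample" t-test, or the Wilcoxon signed-rank test if the data are not normal, two-sided at 0.05. The control children are healthy and untreated (section 2.4.1).

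Section 2.3 asks for at least 15 per group and then states: "Allowing for a 20% dropout rate, we plan to recruit 40 participants (20 participants per group").

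**The concern.** Acute progression is a worsening of the condition that the primary outcome measures. If such a child is withdrawn and has no second YGTSS, the child cannot enter a paired test. The loss then depends on the outcome itself, and the children who remain have a better mean change than all the children treated.

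In a two-arm trial of patients, part of such a loss might occur in both arms and partly cancel. Here the YGTSS comparison is a single-arm before-after contrast, so any selective loss reads directly as improvement. With about 20 treated children, one or two such losses matter.

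This is not only a matter for a statistical analysis plan. Such a plan can define analysis sets and missing-data methods, but it cannot recover week-4 scores that were never collected. Whether assessment continues after withdrawal is a conduct rule and belongs in the protocol.

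**Working it through.** **1. The stated recruitment figure.** From section 2.3: 15 needed per group, 20% dropout. 15 / (1 − 0.20) = 18.75, rounded up to 19; the article recruits 20. In the other direction, 20 × 0.80 = 16, which is at least 15. The figure reproduces within one child per group. It also suggests that the design counts on analysing those who remain, with about 4 of 20 lost.

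**2. What following the text does.**
- Table 1: a child with acute progression is withdrawn.
- Section 2.5: the second YGTSS is taken when the interventions have been completed. For a child withdrawn mid-course, no other scoring occasion is stated.
- Section 3.1.1: the paired test uses change scores, so it needs two scores per child.

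**3. Size of the shift, as an identity.** Let 20 children be treated, with overall mean change zero. If k are lost, the mean among the rest is −k/(20 − k) × (mean change of those lost), with positive meaning worse. For k = 4 the factor is 4/16 = 0.25; for k = 1 it is 1/19 = 0.053.

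**4. Simulation of the false-benefit rate.** Inputs: 20 treated children and two-sided 0.05 (from the article); changes x drawn from N(0, 1) in units of the SD of change, with true mean 0 (assumption). Withdrawal propensity is u = ρx + √(1 − ρ²)e, with e an independent N(0, 1) draw and ρ assumed. The k children with the highest u have no second score. For the rest, t = mean / (s / √(20 − k)), and benefit is declared when t < −t(0.975; 19 − k). There were 40,000 runs. With nobody lost, the mean change is 0.00 and false benefit is 2.5%, as it should be.

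| Children lost | ρ | Mean change (SD) | False significant benefit |
|---|---|---|---|
| 4 | 0 | 0.00 | 2.6% |
| 4 | 0.3 | −0.10 | 6.1% |
| 4 | 0.5 | −0.17 | 10.3% |
| 4 | 0.7 | −0.23 | 17.7% |
| 4 | 1 | −0.33 | 37.9% |
| 2 | 0.5 | −0.09 | 6.2% |
| 2 | 1 | −0.18 | 15.8% |
| 1 | 1 | −0.10 | 7.7% |

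Check against step 3: at k = 4 and ρ = 1, 0.333 / 0.25 = 1.33, so the four lost children average 1.33 SD worse than the true mean. At ρ = 0.5 it is 0.167 / 0.25 = 0.67 SD.

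**5. Direction by ground.**
- Progression: losing these scores moves the estimate toward benefit.
- Prohibited treatment: plausible, since a failing child may seek other treatment. But the term is not defined, and a score taken after effective other treatment could look better.
- Discomfort from needling: undetermined, as it need not track tic severity.
- The remaining three grounds: no stated link to worsening.

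**The case against.** The article never says that a withdrawn child goes unscored. The withdrawal row lists reasons only, and the flow and schedule figures could not be read here. Analysis sets and missing-data handling commonly sit in a full protocol or analysis plan that is not shown, and section 3.1.1 names a test without restricting it to completers. This stands, and it is why the point is conditional. It does not remove the point. The grounds include misdiagnosis, poor cooperation with data collection and voluntary request, so the list reads as leaving the study, and the one stated post-treatment scoring occasion depends on finishing treatment.

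Several stronger readings are tempting and are not supported:
- **That the YGTSS change is biased as a matter of fact.** This would require knowing that withdrawn children are not scored or not analysed.
- **That the false-benefit rate is 38%.** This needs all four losses to be exactly the four worst changes. The 20% is a planning allowance for all causes, with no share assigned to progression, and it is not tied to week 4; there is also a 12-week follow-up.
- **That all three grounds push the same way.** Only progression clearly does.
- **That GSI, recurrence and the prediction model are distorted too.** Nothing links these withdrawals to GSI change. The recurrence denominator is return visits, and the direction there is uncertain. The prediction section says only that data from this study will be used.

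It is also fair to say that tics wax and wane (Introduction), so an uncontrolled before-after change is weak evidence of efficacy even with no dropout, and that the study calls itself exploratory. This limits what is at stake. But YGTSS change is still the declared primary outcome with a significance threshold, and the remedy is cheap.

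**Conclusion.** The point holds in conditional form. Withdrawal for acute progression, a second YGTSS tied to completed treatment and a within-group paired test together can bias the primary result toward benefit, unless withdrawn children are still scored and kept in the analysis.

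The size cannot be derived from the article, which gives no SD of change and no relation between withdrawal and worsening. Over the full assumed range of that relation, with 4 of 20 lost, the overstatement runs from none to 0.33 SD of change. Losing just the single worst child gives 0.10 SD and about three times the nominal error (7.7 / 2.5 = 3.1). The figures rest on normal changes, a true mean of zero and the t-test; the signed-rank alternative was not simulated. The change should be made; the gap is not fatal to the study.

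**What to change.** Leave the rules on when treatment stops as they are, and change only what follows for data:

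1. State that stopping treatment does not end assessment. Score YGTSS and GSI at the scheduled week-4 visit for every treated child whose guardian agrees, and record the reason for withdrawal.
2. Define the primary analysis set as all children given at least one session.
3. Add a sensitivity analysis that sets to no improvement any missing change, and the change of any child withdrawn for progression or prohibited treatment. An observed worsening stays as observed. This also covers the case where a score after other treatment looks favourable.
4. Report withdrawals by reason and timing.

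Section 2.3.1 dates enrolment from April 2022 to March 2023, while section 3.5 says recruitment is under way. If week-4 visits are already over, item 1 is limited to scores actually taken, but items 2 to 4 can still be fixed before analysis.

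The cost is some protocol wording and a few extra assessments at a visit already scheduled. The estimate may turn out less favourable, and a score from a child who changed treatment is harder to interpret, which item 3 addresses.
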